## Abstract

**Background:**

The peanut ball has only been recently used as a support for women labouring with epidurals. The peanut ball is shaped like a peanut and fits snugly between the woman’s legs so that both legs are maintained as opening the pelvic outlet to increase the progress of labour and facilitate descent of the fetal head. Using position changes during labour to enhance widening of the pelvic outlet can be beneficial but a woman who has an epidural is limited in the number of positions she can adopt. No randomised controlled trial has been implemented in Australia to establish the effectiveness of a peanut ball specifically for women using epidurals during labour, and this project addresses this gap. The main aim of this pilot study is to assess the feasibility and practicality of conducting and replicating this trial to a definitive randomised controlled trial (RCT).

**Methods:**

A minimum number of 50 women (25 in each trial arm), who are using an epidural in labour at two hospitals in NSW over a 1-year period, will be recruited and randomly allocated into a group that uses the peanut ball or into a group that does not use the peanut ball. Primary study objectives include assessing the proportion of women willing to be randomised, retention/attrition rates, and with associated reasons. Data will be collected on key clinical outcomes (natural birth rate, length of stay) with means and variances estimated between trial arms. This will inform the appropriate powering of a future definitive RCT. Secondary study objectives will include investigating the completion and acceptability of health and satisfaction surveys and assess the feasibility of conducting an economic evaluation alongside a future trial.

**Discussion:**

This is a two-armed randomised controlled pilot trial. Outcomes from this pilot will inform a larger trial at a tertiary hospital.

**Trial registration:**

Australian New Zealand Clinical Trials Registry, ACTRN12618000662268

**Electronic supplementary material:**

The online version of this article (10.1186/s40814-018-0346-9) contains supplementary material, which is available to authorized users.

## Background

Epidurals have been associated with higher interventions during labour, including a higher incidence of instrumental births [1–3] especially in women having a baby for the first time [4]. Vacuum births have more than doubled in women experiencing epidurals [1]. The National Institute for Health and Care Excellence Guidelines [5] states that there is no evidence pertaining to using a birth ball (the peanut ball falls into the category of a birth ball) during labour, and this project addresses this gap. This guideline [5] recommends that women should be encouraged to move and adopt whatever position she finds comfortable in labour. In fact, there is no evidence in Australia for using a peanut ball specifically for women using epidurals during labour.

The peanut ball is thought to enhance the progress of labour by optimally positioning the fetus in relation to the pelvis [6]. There are multiple benefits associated with maternal position changes, including increased maternal-fetal circulation, decreased pain, improved quality of uterine contractions, facilitation of fetal descent and decreased length of labour [7]. Apart from the physiological benefits of birth, other benefits include less risk of postpartum haemorrhage [8], improved maternal–infant bonding [9], less psychological morbidity postnatally [10], increased rates of successful breastfeeding [9, 11] and improved maternal satisfaction [12]. The woman is also able to independently care for her baby following the birth, whereas women having a caesarean may require more assistance with feeding and general care of the baby. Therefore, widening the pelvic outlet is one way of supporting natural progression of birth.

Three randomised control trials have been implemented in the USA on the use of a peanut ball during labour [13–15]. Of the three randomised control trials in the USA, one of the randomised control trials included women who were scheduled for elective induction of labour and also who used an epidural for labour pain. It was found that the length of time in the first stage of labour was significantly shorter for primiparous (first time having a baby) women using the peanut ball when compared with multiparous (having already had one baby) women and the peanut ball did not make any difference for either group in the time spent pushing [14].

The other randomised control trial showed that women who used the peanut ball during labour had clinically significant lower caesarean section rates, lower instrumental births including forceps and vacuum births, and lower third and fourth degree perineal laceration rates. Even though the findings were clinically significant, they were not statistically significant. There was no difference in the length of stages of labour [15]. One of the randomised control trials showed that using the peanut ball was associated with a significantly lower incidence of caesarean surgery (OR = 0.41, *p* = .04) and is potentially a successful intervention to help progress labour and support vaginal birth for women labouring with an epidural anaesthesia. A small group of nonrandomized labouring women with an epidural who used a peanut ball (*n* = 30) were compared to those who did not (*n* = 22). Lengths of first and second stages of labour were recorded. Results demonstrated a 46-min reduction in first-stage labour and an 11-min reduction in second-stage labour with women who used the peanut ball [13].

The main aim of this pilot study is to assess the feasibility and practicality of conducting and replicating this trial to a definitive randomised controlled trial (RCT) in terms of the rate of willingness to be randomised, retention or attrition rate, staying in the allocated group and reasons for ceasing to use the peanut ball. Data will also be collected on the likely primary and secondary outcome measures to ensure appropriate powering of the future definitive RCT and the minimum clinically important differences between the control and intervention groups. The secondary objectives will investigate completion and acceptability of the health and satisfaction surveys by women who use the peanut ball and all women about their general level of health. Descriptive statistics will be analysed to show key clinical outcomes and the Mann-Whitney *U* and chi-square analyses for differences between the control and intervention groups that will demonstrate an effect size to calculate the appropriate sample size for the definitive RCT. Analyses will be performed blind to group allocation. The study will also include economic measures for costs and health-related quality of life to assess the feasibility of conducting an economic evaluation in a future definitive trial.

There is a need to further investigate these outcomes in Australia as Australia’s practising midwives are a distinct profession compared with obstetric nurses in the USA, so the US results cannot be generalised to Australia. The numerous midwifery-led models of care in Australia [16] (as compared with those of the USA) means that midwives embrace autonomy in their work and promote non-pharmacological or alternative therapies that would impact on their practice if they suggest the peanut ball when working with women with epidurals in labour. Midwifery-led models of care have identified benefits for women and babies with no adverse effects in collaboration with obstetricians and other health professionals [16].

This study will provide evidence about the effect of using the peanut ball for women who have an epidural during labour and be the first of its kind in Australia. It is envisaged that the results of this study will provide evidence for a larger randomised controlled trial in other hospitals in the Nepean and Blue Mountains Local Health District.

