Midwives will record in the Peanut Ball Research Notebook in the birthing unit if the woman changes her mind if she is allocated to the control or intervention group and decides to change to the other group other than the group she has been allocated. It is important to achieve an “intention to treat analysis” and that participants are analysed according to the group they are originally allocated [19].
*To determine why women stopped using the peanut ball*
The Coordinating Investigator will access the Electronic Medical Record to assess why the woman stopped using the peanut ball. It is important to achieve an “intention to treat analysis” to determine whether or not they adhered to or accepted the intervention. The importance of reporting of numbers and the reasons why participants were lost to follow up is necessary to assess the extent to what the intention to treat may lead to and provide an underestimate of the efficacy of the intervention under ideal circumstances [19].
*To assess likely primary and secondary outcome measures to inform sampling size and powering of the definitive RCT*
The main purpose of this pilot study is to assess the feasibility of conducting a full definitive trial and not to generate statistically significant results. Nonetheless, a secondary aim is to inform the sample size calculation to design a full definitive trial. This requires an estimate of a clinically meaningful effect size and variance that can be entered into a sample size calculation. The key primary clinical outcome is the rate of vaginal births, and the key secondary outcome is the length of labour. For this pilot study, a decision was taken to opt for 50 pregnant women (25 in each trial arm) to inform this process. Indeed, a previous pilot study that investigated the use of the peanut ball with similar aims determined that this sample size may actually be sufficient to demonstrate statistically significant findings [13]. Therefore, given the high feasibility of recruiting these numbers of women at the study sites, a decision was then made to aim for 50 pregnant women in total (as a minimum), and so opt for a comprehensive pilot trial to ensure the pilot can confidently test feasibility and also inform the powering of a future definitive trial.

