### Statistical analysis

#### Quantitative data

In terms of the women’s willingness of being randomised into the control or intervention group and assessment of recruitment and attrition rates and staying in the allocated groups, the Coordinating Investigator will access this information from the Peanut Ball Research Notebook and assess the sample size. This information will be estimated as accurately as possible from the critical parameters we wish to estimate [19, 22] that includes the minimum important differences when comparing the means of continuous outcomes and categorical outcomes between the intervention and control groups. The differences between the vaginal birth rate (assessment of likely primary outcome for definitive RCT) and the length of labour (assessment of likely secondary outcome for definitive RCT) will be analysed. Demographics will be reported using descriptive statistics. The Coordinating Investigator will also access women lost to follow up and if women stopped using the peanut ball from the Electronic Medical Record.

The purpose of the pilot is to assess the feasibility of the component elements together to inform a definitive trial. The pilot and sample size of 50 is not intended to be powered to conduct meaningful statistical tests [19]. Nonetheless, and for exposition purposes, standard tests will be conducted and reported. Online survey results will provide complementary data from the woman’s perspective of using the peanut ball during labour and health and quality of life.

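### The definitive trial's effect size is to come from the difference observed between two arms of 25, and the minimum important difference is treated as something the pilot will estimate

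*Protocol article*

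**What the plan says.** Four statements in the protocol article say where the effect size for the definitive trial will come from.

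- Background, analysis: Mann-Whitney and chi-square analyses are planned for "differences between the control and intervention groups that will demonstrate an effect size to calculate the appropriate sample size for the definitive RCT".
- Background, aims: data on the likely outcomes are collected "to ensure appropriate powering of the future definitive RCT and the minimum clinically important differences between the control and intervention groups".
- Measures used to achieve objectives, Primary objectives: on the sample size calculation, "This requires an estimate of a clinically meaningful effect size and variance that can be entered into a sample size calculation". The pilot size follows: "a decision was taken to opt for 50 pregnant women (25 in each trial arm) to inform this process".
- Statistical analysis, Quantitative data: the parameters to be estimated include "the minimum important differences when comparing the means of continuous outcomes and categorical outcomes between the intervention and control groups".

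The outcomes concerned are fixed: "The key primary clinical outcome is the rate of vaginal births, and the key secondary outcome is the length of labour". No value is given for a minimum important difference, and no source outside the pilot is named. The Quantitative data section also concedes that 50 women give too little power for tests to be meaningful. The Primary objectives measures nevertheless say that this number lets the pilot inform the later powering with confidence.

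**The concern.** Two different quantities are run together. An effect size observed in a pilot is a noisy estimate of what the intervention does. A minimum important difference is a judgement about what would be worth detecting, and no comparison of trial arms can estimate it. The Background names the first as the input to the sample size. The other statements use the language of the second but leave the pilot to supply it.

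If the observed difference is used, a pilot that overshoots by chance gives a definitive trial that is too small. A pilot that shows no benefit gives no sample size at all, or could discourage a worthwhile trial. A difference too imprecise to test is also too imprecise to plan on. Informing the later sample size is one of the listed primary objectives, so the source of the target difference should be clear before recruitment starts.

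**Working it through.** **The plan's own figure.** The 50 women are stated as a decision, without alpha, power, rates or SD, so there is no calculation to reproduce.

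**Inputs from the article.** 25 women per arm; vaginal birth as the key outcome and length of labour as the next; an odds ratio of 0.41 for caesarean from an earlier US trial (Background).

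**Assumptions not in the article.** Control caesarean rate 10% to 50%; two-sided 5%; planned power 80%, or 90% as a sensitivity check; the observed difference used directly; the true odds ratio equal to 0.41.

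**Step 1: precision of the observed difference.** With a common vaginal birth rate p, the half-width is 1.96 × √(2p(1−p)/25).
- p = 0.90: 1.96 × √0.0072 = 0.166, or 17 points.
- p = 0.60: 1.96 × √0.0192 = 0.272, or 27 points.
- Length of labour, in SD units: t(0.975; 48 df) × √(2/25) = 2.011 × 0.283 = 0.57 SD.

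**Step 2: the true difference for comparison.** With an odds ratio of 0.41, a control caesarean rate of 20% becomes 0.25 × 0.41 = 0.1025 in odds, or 9.3%, a difference of 10.7 points. Across control rates of 10% to 50% the true difference is 5.6 to 20.9 points. The half-width at those rates is 14.2 to 26.5 points, larger than the true difference at every rate checked.

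**Step 3: one pilot result.** Take 6 of 25 against 2 of 25 caesareans (24% v 8%). The pooled-variance formula gives n = [1.96√(2 × 0.16 × 0.84) + 0.842√(0.24 × 0.76 + 0.08 × 0.92)]² / 0.16² = 1.442²/0.0256, or 82 per arm. If the truth is 20% v 9.3%, the trial needs 171 per arm for 80% power, and 82 per arm gives about 49%. With one caesarean fewer in the control arm (5 v 2), the same formula gives 131 per arm. A single birth moves the answer by 49 women per arm.

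**Step 4: all pilot results.** Every pair of counts from two binomials of size 25 was enumerated. Each favourable pair was put through the same formula, and the true power of the resulting trial was computed at the true rates.

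| Control caesarean rate | Rate at OR 0.41 | No benefit shown | True power under 50%, planned at 80% | True power under 50%, planned at 90% |
|---|---|---|---|---|
| 10% | 4.4% | 31% | 35% | 34% |
| 15% | 6.7% | 24% | 38% | 28% |
| 20% | 9.3% | 19% | 34% | 24% |
| 25% | 12.0% | 15% | 33% | 23% |
| 30% | 14.9% | 13% | 31% | 22% |
| 40% | 21.5% | 10% | 28% | 19% |
| 50% | 29.1% | 8% | 27% | 17% |

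All percentages are of all pilots. The no-benefit share is separate from the under-50% shares, which count only favourable pilots. An unpooled sample-size formula changes the shares by at most about one point.

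**Step 5: sensitivity.** For a true 10-point difference (control rates 20% to 50%), the under-50% share is 38% to 39% at 80% planned power and 27% to 30% at 90%. For length of labour (normal approximation), true power falls below 50% when the pilot overshoots the true effect by a factor of (1.96 + 0.84)/1.96 = 1.43. For true standardised differences of 0.2, 0.3, 0.4 and 0.5, this happens in 38%, 32%, 27% and 22% of pilots.

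**The case against.** The best defence is that the methods text does not bind the trialists to the observed difference. It speaks of a clinically meaningful effect size, says that outcomes will inform the calculation, and describes the tests as done for exposition. No formula is fixed, and the later trial will have its own protocol and justification. This stands in part: the article does not make the observed difference the only input, and the sentence on minimum important differences in the Quantitative data section is too unclear to prove that the two are equated. It does not remove the Background statement, which is explicit. Nor does it supply a value, an outside source or a step for setting the important difference.

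The percentages are also open to challenge. The article says that the US results cannot be carried over to Australia, so the odds ratio of 0.41 is only illustrative, and nothing is stated about the control rate, alpha or power of the later trial. That is fair, and it is why ranges are given.

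Two further criticisms are tempting. A reader might infer that Mann-Whitney and chi-square tests would leave the planners without the quantities a sample size needs. The Abstract says that means and variances will be estimated by arm, and the Background pairs the tests with descriptive statistics, so the ingredients will be there. A reader might also infer from "Outcomes from this pilot will inform a larger trial at a tertiary hospital" that the pilot's event rates cannot apply to the later trial. That the control rate would differ is not in the article, and the Background speaks instead of other hospitals in the same health district.

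**Conclusion.** The concern holds in a limited form. The Background draws the definitive trial's effect size from a difference between two arms of 25, and other sections leave the minimum important difference to the pilot, while the article itself concedes that this number cannot support meaningful tests. The imprecision of 17 to 27 points, or 0.57 SD, needs no assumption about the treatment effect. The shares of misleading pilots do: 27% to 38% at 80% planned power, 17% to 34% at 90%, and a further 8% to 31% with no usable result all rest on the stated assumptions and on mechanical use of the estimate.

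A reader might infer that a third of such pilots would produce an underpowered trial whatever the circumstances. The article does not support that, because the share changes with the true effect, the control rate and the planned power. The case against using the observed difference does not depend on any particular percentage.

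This should be fixed, but it is not a bar to starting. It does not affect participants, trial conduct or the feasibility objectives, and any harm would arise in the later trial. The article also ranks the objective inconsistently, listing it as primary under Objectives and calling it a secondary aim under the measures.

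**What to change.** In the Background, in the Primary objectives measures and in the Quantitative data section, remove the use of the observed between-arm difference as the effect size and make the wording agree. State that:

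1. the target difference for the definitive trial will be a minimum important difference set independently of the pilot result;
2. the pilot will supply only nuisance parameters (vaginal birth rate, SD of length of labour, recruitment, adherence and attrition), each with a confidence interval;
3. planning will allow for the imprecision of those estimates. One option for the SD is its upper 80% confidence limit, which at 48 df is √(48/χ²(0.20; 48)) = 1.10 times the estimate.

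The between-arm difference can still be reported descriptively with its interval. The cost is protocol wording only, and recruitment had not begun when the article was written. The downside is that the definitive sample size may come out larger than an optimistic pilot would suggest.

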## Methods/design

This pilot study will be implemented at the Blue Mountains Anzac District Memorial and Lithgow hospitals, on a group of low-risk women, over a 1-year time period to assess whether there is sufficient evidence for justification for using the peanut ball in a larger randomised controlled study.

Ethics approval for this study was granted in April 2018 by the Nepean Blue Mountains Local Health District Human Research Ethics committee (HREC/18/Nepean/30) and reciprocal approval from Western Sydney University – REDI Reference: RH12693. The trial was registered with the Australian New Zealand Clinical Trials Registry, ACTRN12618000662268, (http://www.ANZCTR.org.au/ACTRN12618000662268.aspx) on the 24th of April at 11:38 am. The study protocol (version 3, March 21, 2018) (see Additional file 1 SPIRIT Protocol) has been designed in accordance with the SPIRIT guidelines (see Additional file 2). Any change to the trial protocol will be communicated to all investigators, reflected in changes to the trial registry and first approved via the ethics committee.

### Setting, recruitment and informed consent

The trial intervention will be conducted in Sydney, Australia, at the Centre for Nursing and Midwifery Research, Nepean hospital, Western Sydney University. The major sites for this pilot study are the Blue Mountains Anzac District Memorial and Lithgow hospitals. Pregnant primiparous (having first baby) and multiparous (having subsequent baby) women who are labouring with an epidural at the Blue Mountains Anzac District Memorial and Lithgow hospitals will be included in the study.

The participants will be identified and approached and consented during labour if they have an epidural.

The women who fit the inclusion criteria will be provided a participant information sheet and then asked to sign a participant consent by the midwife not involved in her care. Once the woman has consented to the project, she has the opportunity to withdraw from the project at any time throughout the course of the project, and not be penalised. The consent will be placed in a research box in the birthing suite by the midwife so that the researcher will be able to recontact the woman to complete an online survey if she used the peanut ball.

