#### Secondary objectives

*To investigate completion of the health and satisfaction surveys*

Health and satisfaction surveysThe Health Questionnaire (EQ-5D) will provide important general physical and mental health information about mobility, self-care, usual activities, (for example, work, study, housework, family or leisure activities), pain, discomfort, anxiety, and depression. EQ-5D is a standardised measure of health status developed by the EuroQol Group in order to provide a simple, generic measure of health for clinical and economic appraisal. The EuroQol Group is a network of international multidisciplinary researchers devoted to the measurement of health status [20]. The Health Questionnaire will also request a single score about level of health experienced on that particular day. The first five questions are measured on a Likert scale, and the last question about perception of health asks the respondent to answer on a scale from 0 to 100 with 0 meaning the worst health they can imagine and 100 meaning the best health they can imagine. It is cognitively undemanding, taking only a few minutes to complete. The survey is applicable to a wide range of health conditions and treatments; it provides a simple descriptive profile and a single index value for health status that can be used in the clinical and economic evaluation of health care as well as in population health surveys. The EQ-5D is designed for self-completion by respondents and is ideally suited for use in postal surveys, in clinics and in face-to-face interviews [20].The survey assessing satisfaction levels obtains information in 13 questions about using the peanut ball in Likert scale responses, yes/no answers and free text responses and takes approximately 5 min to complete. The survey will provide a snapshot about the woman’s experience and enquire about the benefits of using the peanut ball, subsequent use of the peanut ball, whether the woman would recommend using the peanut ball to other women and reasons why, discomfort, specific positions used with the peanut ball, experiencing feelings of empowerment and effect on length of labour and demographic details. The survey was developed in alignment with the results of the previous randomised controlled trials [13–15] and as this research only focuses on quantitative data, it was thought that it was beneficial to obtain some information from women about the comfort, perception and satisfaction about using the peanut ball as complementary evidence to the pilot randomised controlled trial. Face validity has been verified by this survey being reviewed and approved by an ethics committee of expert health research professionals in a local health district in NSW, and the survey will be further validated in this pilot study by comparing responses from both sites by using construct validity and establishing appropriate sample size.

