Both surveys will be distributed to the respondents from an electronic platform—Qualtrics [21] platform—and have been electronically tested to assess the functionality prior to distribution of the online survey. Each survey will be distributed to the participant’s email and de-identified in the computer database. All surveys will be analysed, including those not completed. All of the data collected in this closed survey will be stored in a password-protected computer and will only be accessible by the researchers.
*To assess the feasibility of conducting an economic evaluation alongside a future definitive trial*
The feasibility of collecting data required for an economic evaluation will be tested. For this pilot, we will collect information on health service usage between trial arms, including staff time, medications, procedures and length of stay in hospital. The inclusion of the EQ5D5L will assess the feasibility of incorporating an economic measure of HRQoL, where responses will be converted into ‘health utilities’.
*To measure key clinical outcomes and differences between the control and intervention group*
Details about other birth outcomes will also be collected to determine the baby’s condition, perineal damage, other methods of pain relief used, position of mother and baby during labour, blood loss, cervical dilatation at time of insertion of epidural and evidence of augmentation and/or induction of labour.

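### The only stated recontact route covers women who used the peanut ball, which conflicts with the plan to collect EQ-5D from all women; the two-site comparison also cannot validate the satisfaction survey.

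*Protocol article*

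**What the plan says.** All references are to the protocol article.

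- **Setting, recruitment and informed consent.** The midwife places the signed consent in a research box "so that the researcher will be able to recontact the woman to complete an online survey if she used the peanut ball". The survey is singular and not named. The condition is use of the ball, not allocation to it.
- **Background, statement of aims.** The secondary objectives cover "health and satisfaction surveys by women who use the peanut ball and all women about their general level of health". This separates two groups of respondents: users for the satisfaction survey, everyone for general health.
- **Measures used to achieve objectives, Secondary objectives.** On distribution: "Each survey will be distributed to the participant’s email and de-identified in the computer database", with no limit by arm or by use. On the economic objective: "The inclusion of the EQ5D5L will assess the feasibility of incorporating an economic measure of HRQoL", with responses converted to utilities, alongside resource use collected in both arms.
- **Same section, on the satisfaction survey.** "The survey assessing satisfaction levels obtains information in 13 questions about using the peanut ball". On its validation: "the survey will be further validated in this pilot study by comparing responses from both sites by using construct validity".
- **Measures used to achieve objectives, Primary objectives.** Control women who decide to use the ball are foreseen and their reasons are recorded. Analysis is to follow original allocation.

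**The concern.** The Background and the distribution paragraph state an intention. The consent section states what a site and the researcher will actually do. Where the two differ, the procedure usually decides which data exist.

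A survey list built from the consent section would be selected by treatment received. It would leave out control women who stayed in their arm and women allocated to the ball who never used it, and it would include control women who crossed over. For EQ-5D this matters in two ways. Survey completion and the variance of utilities could not be estimated in the control arm. The few control responses would come only from women who departed from their allocation, which does not fit analysis by original allocation. Health status in the postnatal period cannot be recovered later.

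The validation statement is a smaller, separate matter. It promises evidence of construct validity from a comparison that cannot supply it.

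**Working it through.** **No planned figure is affected.** The article gives no alpha, power, effect size or standard deviation behind its sample size. The only check available is 25 + 25 = 50, which agrees. The 50 is a minimum, so the counts below are nominal.

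**Step 1. Who is sent EQ-5D under each reading.**

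| Reading | Ball arm | Control arm | Total |
|---|---|---|---|
| Background and distribution paragraph govern EQ-5D | 25 | 25 | 50 |
| Consent section governs both surveys, full adherence | 25 | 0 | 25 |
| Consent section governs both surveys, non-use *a*, crossover *b* | 25(1 − *a*) | 25*b* | 25(1 − *a*) + 25*b* |

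The article gives no rates for *a* or *b*. Assume 0 to 20% for each:
- ball arm: 25 × 0.8 = 20, up to 25
- control arm: 0, up to 25 × 0.2 = 5, all of them crossovers
- total: 20 + 0 = 20, up to 25 + 5 = 30

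On the literal reading, then, 20 to 30 of the 50 women would not be invited, and 20 to 25 of these would be control women.

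**Step 2. What is lost for survey completion.** The approximate 95% half-width for a completion rate *p* is 1.96 × √(*p*(1 − *p*)/*n*). With *p* assumed between 50% and 90%:
- *n* = 50: 1.96 × √(0.25/50) = 13.9 points; 1.96 × √(0.09/50) = 8.3 points
- *n* = 25: 1.96 × √(0.25/25) = 19.6 points; 1.96 × √(0.09/25) = 11.8 points

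With all women invited, each arm gives a rough estimate (the *n* = 25 line) and the trial as a whole a better one (the *n* = 50 line). On the literal reading with no crossover, control has *n* = 0 and no estimate exists, either of completion or of utility variance.

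**Step 3. The satisfaction survey.** The use condition applies here on either reading. Women who tried the ball and stopped did use it, so they are included. Never-users are not, and control crossovers are. The responses therefore describe users. They do not represent all women allocated to the ball, and they are not a comparison between arms.

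**Step 4. The validation statement.** Construct validity asks whether the items measure what they are meant to measure. Similar answers at two sites can arise whether or not they do. Different answers may reflect different women, midwives or practice. Neither result bears on the question, and more women would not change that.

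The comparison would also be weak as a test. Assume about 25 users, split 12 and 13. For a two-sided 5% test with 80% power and 23 degrees of freedom, the detectable standardised difference is (2.069 + 0.858) × √(1/12 + 1/13) = 2.927 × 0.4003 = 1.17.

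**The case against.** The strongest reply is that the passages can be read together. The consent section speaks of one unnamed survey, conditional on use. The Qualitative data section uses the term online survey for the satisfaction questionnaire. If the consent section means only that one, it agrees with the Background, and EQ-5D goes to everyone by email. This reading is plausible. It is why a reader who infers that the control arm will yield no EQ-5D data goes further than the article allows: the Background names all women, and the distribution paragraph has no restriction. Even on the literal reading, control crossovers would be contacted.

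Two other inferences also go too far. One is that the feasibility of an economic evaluation would be wholly untested. Staff time, medications, procedures and length of stay are collected in both arms and do not depend on the survey. The other is that acceptability of the ball is biased upward by some stated amount. The acceptability objective concerns the surveys; stopping and switching are primary objectives recorded in the research notebook and the medical record. Limiting the satisfaction survey to users is declared and follows from its content. The article gives no satisfaction rates from which a bias could be computed.

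The full protocol is an additional file and may settle the survey logistics. What remains is that the only recontact purpose printed here excludes non-users, while two other parts of the same article need them. The favourable reading requires the reader to supply a word that the consent section does not contain.

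**Conclusion.** The finding is a conflict between the stated recontact procedure and the stated EQ-5D respondents. It does not show that control EQ-5D data will be missing. If the procedure were applied literally to both surveys, control invitations would fall from 25 of 25 to 0 of 25 without crossover, or at most 5 of 25 at an assumed 20% crossover. Control-arm completion and utility variance would then not be usefully estimable. That would defeat the control-arm part of the survey-completion objective and the utility part of the economic objective. Resource-use feasibility would be unaffected.

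The user-only satisfaction survey is acceptable if it is reported as such. The validation claim is wrong as written, whatever the number of respondents; the figure of 1.17 is illustrative and rests on an assumed 12 and 13 split.

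The conflict should be resolved before recruitment, because the loss could not be repaired afterwards.

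**What to change.** 1. **Setting, recruitment and informed consent.** State that every randomised woman is recontacted for EQ-5D-5L at the same postnatal time, whatever her allocation or use of the ball.
2. **Satisfaction survey.** Keep it for women who used the ball, and say explicitly that this includes those who stopped early and control women who crossed over. Report it by allocated arm, with the numbers allocated, using and responding, and describe it as the experience of users only.
3. **Secondary objectives, survey validation.** Delete the claim that comparing the two sites will validate the survey. Report the survey as unvalidated beyond face validity, with item completion and response distributions.

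The cost is about 25 more emailed questionnaires and a minor ethics submission; Methods/design requires protocol changes to be approved by the ethics committee first and reflected in the registry. Trial status says that recruitment had not begun, so no data already collected would be affected.
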